#### **2.2.2 Exclusion Criteria**

1. Age <18 years
2. On-going treatment with anticoagulant drugs
3. Platelet count < 100.000/mm^3
4. History of heparin-induced thrombocytopenia
5. Allergy to sodium enoxaparine or other LMWH, unfractionated heparin or methylprednisolone;
6. Active bleeding or on-going clinical condition deemed at high risk of bleeding contraindicating anticoagulant treatment
7. Recent (in the last 1 month prior to randomization) brain, spinal or ophthalmic surgery
8. Chronic assumption of oral corticosteroids
9. Pregnancy or breastfeeding or positive pregnancy test. In childbearing age women, before inclusion, a pregnancy test will be performed if not available;
10. Clinical decision to withhold life-sustaining treatment or “too sick to benefit”;
11. Presence of other severe diseases impairing life expectancy (e.g. patients are not expected to survive 28 days given their pre-existing medical condition);
12. Lack or withdrawal of informed consent.

### **2.3 INTERVENTIONS**

Patients who satisfy all inclusion criteria and no exclusion criteria will be randomly assigned to a LMWH group (Group 1), LMWH+steroids (group 2) or UFH+steroid group (Group 3).

The study is conceived as open-label: the patients and all the health-care personnel will be aware of the assigned group. The treatments will be initiated as soon as possible after randomization (maximum allowed starting time 12h after randomization). In both groups, before enrolment in the study it will be allowed the

administration of low-dosages steroids for ARDS treatment (maximum 320 mg of Methylprednisolone per day for a maximum of 2 days).

**Group 1** (LMWH group): Patients in this group will be administered enoxaparin at standard prophylactic dose (i.e., 4000 UI once day, increased to 6000 UI once day for patients weighting more than 90 kg).

The treatment with enoxaparin will be initiated as soon as possible after randomization (maximum allowed starting time 12h after randomization). The treatment will be administered subcutaneously, daily up to ICU discharge. After ICU discharge it may be continued or interrupted in the destination ward up to clinical judgement of the attending physician.

**Group 2** (LMWH + steroids group): Patients in this group will receive enoxaparin and methylprednisolone.

Enoxaparin will be administered at standard prophylactic dose (i.e., 4000 UI once day, increased to 6000 UI once day for patients weighting more than 90 kg). The treatment will be administered subcutaneously daily up to ICU discharge. After ICU discharge it may be continued or interrupted in the destination ward up to clinical judgement of the attending physician. Methylprednisolone will be administered intravenously with an initial bolus of 0,5 mg/kg followed by administration of 0,5 mg/kg 4 times daily for 7 days, 0,5 mg/kg 3 times daily from day 8 to day 10, 0,5 mg/kg 2 times daily at days 11 and 12 and 0,5 mg/kg once daily at days 13 and 14.

**Group 3** (UFH + steroid group): Patients in this group will receive unfractionated heparin and methylprednisolone. Unfractionated heparin will be administered intravenously at therapeutic doses. The infusion will be started at an infusion rate of 18 IU/kg/hour and then modified to attain APTT Ratio in the range 1.5-2.0. aPTT will be periodically checked at intervals no longer than 12 hours. The treatment with unfractionated heparin will be administered up to ICU discharge. After ICU discharge anticoagulant therapy may be interrupted or switched to prophylaxis with LMWH in the destination ward up to clinical judgement of the attending physician. Methylprednisolone will be administered intravenously with an initial bolus of 0,5 mg/kg followed by administration of 0,5 mg/kg 4 times daily for 7 days, 0,5 mg/kg 3 times daily from day 8 to day 10, 0,5 mg/kg 2 times daily at days 11 and 12 and 0,5 mg/kg once daily at days 13 and 14. The dosage and time schedule were defined accordingly with dosage used in the large trial on ARDS by Steinberg KP et al (33)

**Concomitant medications:**

Depending on their clinical status, patients will be treated according to the principles of the Good Clinical Practice and clinical judgement of the attending physician. No other pharmacological therapy or treatment will be influenced from the study protocol. There are no restrictions to concomitant treatments provided to patients in this study. All relevant concomitant medications and treatments taken or administered in the 24 hours before screening and during the study period will be recorded.

Upon clinical judgement of the attending physicians, the patients can receive rescue administration of high- dose steroids or immune-modulatory drugs. Need and timing of rescue treatments administration will be recorded.

**Criteria for discontinuing or modifying allocated interventions:**

The duration of study therapy will be until ICU discharge for LMWH and UFH and 7 days for Methylprednisolone. Patients may be prematurely discontinued from study protocol at the discretion of the Investigator, should any untoward effect occur (including an AE or clinically significant laboratory abnormality that, in the opinion of the Investigator, warrants the subject's permanent discontinuation of study protocol-directed care).

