### **2.6 SAMPLE SIZE**

The target sample size is based on the hypothesis that the combined use of UHF and steroids versus the LMWH group will significantly reduce the risk of 28-day death. The overall sample size in this study is expected to be 210 with a randomization 1:1:1. Assuming an alpha of 2.5% (two tailed) and mortality rate in LMWH group of 50%, as indicated from initial studies of ICU patients, the study will have an 80% power to detect at least a 25 % absolute reduction in the risk of death between:

a) LMHW + steroids group and LMWH group

or

b) UHF + steroids group and LMWH group

The study has not been sized to assess the difference between LMHW + steroids group and UHF + steroids group, therefore the results obtained from this comparison will need to be interpreted with caution and will need further adequately sized studies to be confirmed.

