### **5.3 Auditing**

The principal investigator and the SC will provide all the necessary information and material to the participating centres in order to standardize all the protocol-related procedures and to avoid unexpected variability between centres. A preliminary audit between the coordinating centre and the satellite centres will be performed before to start the recruitment phase to offer the major consensus and homogeneity possible. Printed and electronic informative material (complete original protocol, informed consent modules, informative modules for patients and relatives, recruitment check-list, graphic timeline of interventions and visits, order-list for physicians and nurses) will be distributed to every centre.

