#### APPENDIX 4: Study timeline

| Time-points                                               |                           | Day-0                                                                                                                                                        | From Day 0 to Say 28 | Day-28 | ICU discharge | Hospital discharge |
|-----------------------------------------------------------|---------------------------|--------------------------------------------------------------------------------------------------------------------------------------------------------------|----------------------|--------|---------------|--------------------|
| Eligibility Screen A                           |                           | X                                                                                                                                                            |                      |        |               |                    |
| Informed consent                                          |                           | X
or as soon as feasible                                                                                                                                  |                      |        |               |                    |
| Allocation                                                |                           | X                                                                                                                                                            |                      |        |               |                    |
| Treatment:                                                | LMWH (group 1)            | 
 
• Enoxaparine from day 0 to ICU discharge
 
                                                                  |                      |        |               |                    |
|                                                           | LMWH + steroids (group 2) | 
 
• Enoxaparine: from day 0 to ICU discharge
 
• Methylprednisolone: from day 0 to day 14
 
             |                      |        |               |                    |

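### The discontinuation paragraph gives methylprednisolone 7 days, but the dosing schedule and study timeline give 14 days with a taper

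*Protocol*

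**What the plan says.** Section 2.3 of the Protocol gives Group 2 (LMWH plus steroids) and Group 3 (UFH plus steroids) the same methylprednisolone schedule. After a 0.5 mg/kg bolus, it continues as "0,5 mg/kg 4 times daily for 7 days, 0,5 mg/kg 3 times daily from day 8 to day 10", and then "0,5 mg/kg 2 times daily at days 11 and 12 and 0,5 mg/kg once daily at days 13 and 14". The Group 3 paragraph adds that dose and timing were taken from a large ARDS trial of corticosteroids.

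Appendix 4 repeats the course length in the treatment rows for both groups: "Methylprednisolone: from day 0 to day 14".

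Later in section 2.3, the paragraph on criteria for discontinuing or modifying allocated interventions opens with: "The duration of study therapy will be until ICU discharge for LMWH and UFH and 7 days for Methylprednisolone". The rest of that paragraph concerns early withdrawal from study treatment at the investigator's discretion.

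**The concern.** The Protocol gives two durations for the same drug. The shorter one stands without qualification under the heading where staff would look for stopping rules. It is not presented as the length of the full-dose phase. It is called the duration of study therapy, and the same sentence gives the heparins their complete duration, so a reader will take the methylprednisolone figure as complete too.

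Two things are at stake:

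- **Treatment.** A site that took the sentence as the stop date would end methylprednisolone abruptly from the full daily dose and omit the step-down, in critically ill patients.
- **Adherence.** A patient whose steroid ends after day 7 has completed treatment under one paragraph and stopped early under the other. Section 4.1 asks the monitor to verify adherence to the protocol, and here the protocol sets two standards.

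**Working it through.** **Inputs.** All come from the Protocol: the dosing schedule for Groups 2 and 3 (section 2.3), the treatment rows of Appendix 4, the 7-day sentence (section 2.3, discontinuation paragraph), and the planned total and allocation ratio (section 2.6).

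**Where the 7 days comes from.** It equals the length of the four-times-daily phase alone. It cannot be reproduced as the length of the whole course.

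**Length of the scheduled course.** 7 (days 1–7) + 3 (days 8–10) + 2 (days 11–12) + 2 (days 13–14) = 14 days, which matches the end point in Appendix 4.

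**Doses and cumulative dose, at 0.5 mg/kg each:**

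| Phase | Doses | mg/kg | Daily dose (mg/kg) |
|---|---|---|---|
| Bolus | 1 | 0.5 | – |
| Days 1–7, four times daily | 4 × 7 = 28 | 14.0 | 2.0 |
| Days 8–10, three times daily | 3 × 3 = 9 | 4.5 | 1.5 |
| Days 11–12, twice daily | 2 × 2 = 4 | 2.0 | 1.0 |
| Days 13–14, once daily | 1 × 2 = 2 | 1.0 | 0.5 |
| Total | 44 | 22.0 | |

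**If stopped after day 7.**

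- Given: 1 + 28 = 29 doses, or 14.5 mg/kg.
- Omitted: 9 + 4 + 2 = 15 doses, or 22.0 − 14.5 = 7.5 mg/kg.
- Share omitted: 7.5 / 22.0 = 15 / 44 = 34%, which is the entire taper.
- The daily dose goes from 2.0 mg/kg to zero instead of stepping through 1.5, 1.0 and 0.5 mg/kg.

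**In milligrams.** The Protocol gives no body weights, so 60 to 100 kg is an assumption. The daily dose at the stop is 2.0 × weight: 120, 160 and 200 mg at 60, 80 and 100 kg. The amount not given is 7.5 × weight: 450, 600 and 750 mg.

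**Patients in scope.** 210 / 3 = 70 per arm, and two arms receive methylprednisolone, so 2 × 70 = 140. This counts patients allocated, and is therefore an upper limit on how many could be affected.

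**Whether the sample size depends on this.** Section 2.6 assumes 50% against 25% mortality, a two-sided alpha of 2.5% and 80% power. With the usual two-proportion formula (pooled variance under the null), n = [2.241 × √(2 × 0.375 × 0.625) + 0.842 × √(0.25 + 0.1875)]² / 0.25² ≈ 70 per arm, or 210 in total. The planned number reproduces, and treatment duration does not enter it.

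**Which text is right.** Two dosing paragraphs and two timeline rows agree on 14 days. Only the dosing paragraphs state dose and frequency. The 7-day sentence stands alone.

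**The case against.** The strongest reply is that nobody is likely to be misled. The discontinuation paragraph contains no dose, so methylprednisolone cannot be ordered from it. Whoever writes the order must go to the Group 2 or Group 3 paragraph, where the taper follows the 7-day phase in the same sentence. The 7-day figure is a one-line summary in a paragraph mainly about untoward effects. Staff training and the printed material described in section 5.3 ("graphic timeline of interventions and visits, order-list for physicians and nurses") may already carry the 14-day course. The primary analysis is by intention to treat and takes in all enrolled patients however long they were treated, and the Protocol defines no per-protocol or completer set. The figure of 140 also overstates exposure, because only patients alive and still on study steroid at day 7 could lose the taper.

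Much of this stands. The intent is clear, no divergence between sites is shown, the primary comparison is untouched, and 140 is a ceiling. It limits how much harm to expect, but it does not remove a wrong instruction from the current text. The content of the site material is not shown, and the Protocol is its source. The lack of a completer set does not make the ambiguity idle either, because the monitor still needs a single duration to check adherence against.

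**Conclusion.** The contradiction is real and should be corrected. The Protocol gives methylprednisolone 7 days in one sentence and 14 days in four other places, with nothing to reconcile them. The evident intent is 14 days including the taper, subject to confirmation by the sponsor.

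Followed literally, the shorter figure would cost a patient the whole taper, about a third of the cumulative dose. This is the most any one patient could lose. It assumes that the patient is alive and on study steroid at day 7 and that the site acts on the 7-day sentence. It is not an estimate of an effect at trial level, and the milligram figures depend on the assumed body weights.

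The fault is one of treatment instruction and adherence checking. It does not alter the design, the sample size or the main analysis.

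**What to change.** Once the sponsor confirms, change the methylprednisolone part of the sentence to say that it is given through day 14 as scheduled in section 2.3: full dose for 7 days, then the taper on days 8 to 14. A reference to the schedule is safer than replacing 7 days with 14 days alone, because Appendix 4 starts counting at day 0 and a bare count would leave open whether that day is included.

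Then tell sites that the Group 2 and Group 3 dosing paragraphs govern, and check that the order-list and graphic timeline sent to centres carry that schedule. If any patients have already been treated, record the course each actually received.

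The cost is a one-line amendment, a site notice and a check of printed material.

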## **Strategies to improve adherence to protocols**

The site PIs will take primary responsibility for training local staff and for ensuring that protocol compliance is achieved.

## **2.4 OUTCOMES**

### **2.4.1 Primary Endpoint:**

- All-cause mortality at day 28.

### **2.4.2 Secondary Endpoints:**

- Ventilation free days (VFDs) at day 28, defined as the total number of days that patient is alive and free of ventilation between randomisation and day 28 (censored at hospital discharge). Ventilation is considered as positive pressure ventilation, either invasive or non-invasive. Periods of assisted breathing lasting less than 24 hours for surgical procedures will not count against the ventilation free days calculation;
- Need of rescue administration of high-dose steroids or immune-modulatory drugs;
- Occurrence of switch from non-invasive to invasive mechanical ventilation during ICU-stay;
- Delay from start of non-invasive ventilation to switch to invasive ventilation;
- All-cause mortality at ICU discharge and hospital discharge;
- ICU free days (IFDs) at day 28, defined as the total number of days between ICU discharge and day 28. If death occurs during the ICU stay before day 28 the ICU free days calculation will be 0. The ICU readmission before day 28 after randomization will be considered;
- Occurrence of new infections from randomization to day 28; including infections by Candida, Aspergillus, Adenovirus, Herpes Virus e Citomegalovirus
- Occurrence of new organ dysfunction and grade of dysfunction during ICU stay. Organ dysfunction is defined as a Sequential Organ Failure Assessment (SOFA) score  $\geq 3$  occurring after randomization, grade of dysfunction is measured with SOFA score (see SOFA score in APPENDIX 4) daily from randomization to ICU discharge (censored at day 28);
- Objectively confirmed venous thromboembolism, stroke or myocardial infarction;
- Occurrence of major bleeding (safety end point), defined as transfusion of 2 or more units of packed red blood cells in a day, bleeding that occurs in at least one of the following critical sites [intracranial, intraspinal, intraocular (within the corpus of the eye; thus, a conjunctival bleed is not an intraocular bleed), pericardial, intra-articular, intramuscular with compartment syndrome, or retroperitoneal], bleeding that necessitates surgical intervention and bleeding that is fatal (defined as a bleeding event that was the primary cause of death or contributed directly to death);
- Occurrence of clinically relevant non-major bleeding (safety end point) defined as acute clinically overt bleeding that does not meet the criteria for major and consists of any bleeding compromising hemodynamics; spontaneous hematoma larger than 25 cm^2, or 100 cm^2, intramuscular hematoma documented by ultrasonography, haematuria that was macroscopic and was spontaneous or lasted for more than 24 hours after invasive procedures; haemoptysis, hematemesis or spontaneous rectal bleeding requiring endoscopy or other medical intervention or any other bleeding requiring temporary cessation of a study drug.

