## **4.2 STATISTICAL METHODS**

### **4.2.1 Methods for statistical analysis**

All patients enrolled in the study will be entered in the full analysis set independently of his/her treatment time. The intention to treat population will be considered for primary analysis. A descriptive statistical analysis will be performed to describe every relevant variable. In general, categorical data will be presented using counts and percentages, whilst continuous variables will be presented using the number of patients, mean, standard deviation, median, minimum, and maximum. Denominators for calculation of percentages will be taken as the number of non-missing responses in the specified analysis population and treatment group unless otherwise stated, and percentages will be rounded to one decimal. Minima and maxima will usually be reported to the same level of accuracy as the raw data; means, medians and standard deviations will be presented to one further decimal place; standard errors (if presented) will be presented to 2 decimal places more than the raw data. 97.5 % confidence interval will be calculated for primary outcome and for the relevant secondary ones. All data recorded in the CRF will be listed. Distribution of SAPSII and SOFA score (total and for single organ) at admission, P/F ratio distribution at baseline and at day 3, biomarkers PCR, PCT and IL-6 P/F ratio distribution at baseline and at day 3 will be summarized.

The comparison between

1. LMHW + steroids group and LMWH group
2. UHF + steroids group and LMWH group

with binary outcomes will be performed by using Relative Risks (RRs), whereas for continuous data, the difference of means (DMs) will be used. Comparisons involving time to event data will be displayed by using Kaplan-Maier survival curves and summarised by Hazard Ratios (HRs).

All measures of association will be presented with their confidence intervals. A result will be considered as statistically significant if its p-values will be less than 0.025 (2.5%).

The analyses will be performed by using STATA software.

As the study has not been sized to assess the difference between LMHW + steroids group and UHF + steroids group, the results obtained from this comparison will be reported and will be interpreted with caution. The main analyses will not take into account the factors of stratification.

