- Routine laboratory test parameters for organ function assessment: haemoglobin, platelets count, white blood cells count, troponin, coagulative parameters (INR, PT, aPTT), parameters for liver (AST, ALT, bilirubin) and renal function (creatinine) will be recorded daily from inclusion to day 7 and then at day 14, 21, 28, censored at ICU discharge;
- Blood cells count, C-reactive protein (CRP) and procalcitonin (PCT), IL-6, immunoglobulins titers (IgG, IgA, IgM) will be recorded daily from inclusion to day 7 and then at day 14, 21 and 28, censored at ICU discharge;
- Beta-D Glucan in the blood and/or Galactomannan in the BAL will be recorded at admission and then every 3-5 days, censored at ICU discharge
- Ventilation mode (spontaneous breathing or mechanical ventilation), inspired oxygen fraction and arterial blood gas analysis parameters will be recorded daily from inclusion to ICU discharge, censored at day 28;
  - Adjunctive treatment such as pronation cycles, Nitric Oxide or ECMO will be recorded daily from inclusion to ICU discharge from (censored at day 28);
- New blood, respiratory and urinary-tract infections and the implicated microorganisms will be recorded from randomization to day 28;
- Viral reactivation measured by ADENOVIRUS, HSV e CMV DNA titres will be recorded from randomization to day 28, censored at ICU discharge;
- Need of renal replacement therapy: from randomization to 28 days, censored at ICU discharge.

D) Primary Outcome:

- All-cause mortality will be measured at day 28.

E) Secondary Outcomes:

- All-cause mortality will be measured at ICU discharge and hospital discharge
- SOFA score and its components will be recorded daily from randomization to ICU discharge (censored at day 28);
- Ventilation free days (VFDs) at day 28, measured at day 28;
- ICU free days (IFDs) at day 28, measured at day 28;
- Need of rescue administration of high-dose steroids or immune-modulatory drugs, measured from randomization to ICU discharge, censored at day 28;
- Switch from non-invasive to invasive mechanical ventilation from randomization to ICU discharge, censored at day 28;
- Occurrence of new infections will be recorded from randomization to day 28;
- Occurrence of objectively confirmed venous thromboembolism, stroke or myocardial infarction will be recorded from randomization to day 28;
- Occurrence of protocol related adverse events (see chapter 5.2) at day 28 (safety endpoint).

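### ICU-free days give full credit after a death on the ward, and ventilation-free days, read literally, stop accruing at live hospital discharge; both definitions need rewording

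*Protocol*

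**What the plan says.** Protocol section 2.4.2 defines the two counts.

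- **VFDs:** days "alive and free of ventilation between randomisation and day 28 (censored at hospital discharge"). What counts as ventilation is also fixed: "Ventilation is considered as positive pressure ventilation, either invasive or non-invasive". No special score is given for patients who die.
- **ICU-free days:** "defined as the total number of days between ICU discharge and day 28". The definition does not require the patient to be alive. The only death rule is "If death occurs during the ICU stay before day 28 the ICU free days calculation will be 0". On readmission it says "The ICU readmission before day 28 after randomization will be considered", without a method.

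Appendix 4 adds only the timing: "Ventilation free days (VFDs) at day 28, measured at day 28" and "ICU free days (IFDs) at day 28, measured at day 28". It repeats neither the discharge cut-off nor a death rule.

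Section 4.2.1 says that "for continuous data, the difference of means (DMs) will be used", so the day counts enter the comparison as plain numbers.

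**The concern.** A free-days score should rise as the patient does better. Each definition has a place where it may not.

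- **ICU-free days.** The zero covers death in one location only. A patient who dies after leaving the ICU keeps every day up to day 28, including days after death.
- **VFDs.** Censoring is a concept for time-to-event data. Applied to a count, it most naturally means that no days are added after the cut-off. A patient sent home alive then loses the remaining days, while a patient who stays in hospital keeps them.

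A difference of means carries these scores straight into the treatment estimate. An arm with more ward deaths would pay no ICU-free-day penalty for them. On the literal reading of VFDs, an arm with faster discharge would lose days because of the faster discharge.

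**Working it through.** **The plan's own figure.** The protocol states no size or power for VFDs or ICU-free days. Its only related figure is the 210 in section 2.6, for 28-day mortality. With 50% v 25%, two-sided alpha 0.025, 80% power and pooled variance:

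n = [2.2414 × √(2 × 0.375 × 0.625) + 0.8416 × √(0.25 + 0.1875)]² / 0.25² = 69.97, so 70 per arm and 3 × 70 = 210.

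The figure reproduces and does not depend on either definition discussed here.

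**Single patients, section 2.4.2 applied literally.** The courses are assumed. VFDs = (earliest of day 28, death, hospital discharge) - day off ventilation. ICU-free days = 28 - day of ICU discharge, or 0 if death occurs in the ICU.

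ICU-free days:
- ICU discharge day 10, ward death day 12: 28 - 10 = 18
- ICU discharge day 10, survivor: 28 - 10 = 18
- ICU discharge day 20, survivor: 28 - 20 = 8

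VFDs:
- Off ventilation day 8, home alive day 15: 15 - 8 = 7
- Off ventilation day 8, in hospital on day 28: 28 - 8 = 20

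**Would an alive condition alone repair ICU-free days?** Take ICU discharge on day 8 and ward death on day 20. Counting only days alive outside the ICU gives 20 - 8 = 12, still above the survivor with 8. Only a score of 0 for death ranks it lowest.

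**Effect on a mean difference in VFDs, literal reading.** The documents give no ventilation or discharge times, so all of these are assumptions:
- Time to end of ventilation averages 14 days (control) v 11 days (treatment). Times are gamma distributed with shape 4, as are the times from end of ventilation to hospital discharge.
- Patients who die score 0, to isolate the discharge rule. The protocol itself would credit days before death.
- Arm mean = (1 - mortality) × mean survivor score. The survivor score is max(0, 28 - T) for the full count, and max(0, min(28, T + D) - T) when the count stops at discharge. T is time to end of ventilation and D is time from then to discharge.

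With mortality 50% in both arms, the full count gives 7.1 v 8.5, a benefit of 1.4 days. Stopping at discharge gives:

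| Mean time from end of ventilation to discharge, control v treatment | Difference (treatment - control) |
|---|---|
| 12 v 12 days | +0.6 |
| 12 v 11 days | +0.2 |
| 12 v 10 days | -0.1 |
| 12 v 7 days | -1.3 |
| 7 v 7 days | +0.3 |
| 20 v 15 days | about +0.1 |

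With the mortality planned in section 2.6 (50% v 25%) and 12 v 7 days, the full count gives 7.1 v 12.8, a benefit of 5.7 days. Stopping at discharge gives 4.7 v 5.0, a benefit of 0.3.

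**The case against.** **A second reading of the VFD text.** Elsewhere in section 2.4 and in Appendix 4 the protocol uses the same term for the point at which an item stops being recorded. On that usage ventilation status is simply not followed after discharge, and a patient at home may still accrue days. The definition also runs to day 28, and Appendix 4 measures VFDs at day 28 with no cut-off. The patient home on day 15 would then score 28 - 8 = 20. This stands as a possible reading, but the text does not state it, and the two readings give 7 and 20 for one patient.

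**Death handling as convention.** Days alive and free of ventilation is a coherent endpoint, and scoring every death 0 is one convention among several. This also stands, so a common death rule is a preference. It does not excuse ICU-free days, where the protocol chose to score death as 0 and covered only deaths in the ICU. The VFD convention also has a cost on either reading: off ventilation on day 6 and dead in hospital on day 20 scores 14, above a survivor off on day 16 and still in hospital on day 28 (12).

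**Left to the analysis plan.** Derivation details are often settled there. But the ICU-free-day death rule is stated here, so an analysis plan would have to override it.

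**A stronger inference to avoid.** A reader might conclude that both endpoints will favour the worse arm. The documents do not support that. The VFD sign changes only under some assumed stays, and with the planned mortality difference it did not change in the case tried. No reversal has been shown for ICU-free days. Deaths are also reported separately at day 28, ICU discharge and hospital discharge, so ward deaths would not be hidden.

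**Conclusion.** The ICU-free-day fault follows directly from the text: a death after ICU discharge scores as if the patient had survived, and nothing in section 4.2.1 or Appendix 4 corrects it. Its effect on an arm mean cannot be calculated, because the documents give no rate of ward death before day 28.

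The VFD fault is certain only as an ambiguity. On the literal reading, faster discharge attenuates a VFD benefit and sometimes reverses it: a 1.4-day benefit fell to between +0.6 and -1.3 days at equal mortality with a control stay of 12 days, and a 5.7-day benefit fell to +0.3 at 50% v 25% mortality and 12 v 7 days. These sizes rest on assumed distributions and stays and show a mechanism; they are not forecasts. If only recording was meant to stop, the discharge problem disappears once the text says so.

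This should be fixed before analysis, but it does not threaten the trial's main result. Both are secondary endpoints, and the primary endpoint and the 210 patients are unaffected.

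**What to change.** Reword the two definitions in section 2.4.2 and carry them into the analysis plan.

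- **ICU-free days:** days alive and outside the ICU from randomisation to day 28, with days of ICU readmission subtracted, and 0 for any death by day 28 in or out of the ICU.
- **VFDs:** delete the discharge censoring. Count days after live discharge up to day 28 as ventilation-free unless ventilation or death is known to have occurred.
- **Death rule:** preferably the same for both endpoints, namely 0 for death by day 28.

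The cost is an amendment to wording. Vital status at day 28 is already needed for the primary endpoint, so the death rule needs no new data. The protocol describes no post-discharge contact about ventilation. If the sponsor wants ventilation after discharge verified rather than presumed absent, that would be a small extra data item.
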